## Abstract

**Background:**

The high incidence of workplace violence (WPV) in clinical mental health settings has caused a series of negative impacts on nurses, which has subsequently increased public concern. De-escalation (DE) is recommended as a training program which aims at providing nurses with skills and strategies to more effectively respond and manage WPV. Very few studies have examined the effectiveness of DE training, with current studies possessing various limitations due to their design and small sample sizes. By using a cluster randomized controlled design, the proposed study aims to evaluate the effectiveness of a CRCSE-based DE training programs among psychiatric nurses.

**Method:**

A cluster randomized controlled trial, with a 6-month follow-up period after the end of the intervention, will be conducted among psychiatric hospitals in Guangdong, China. The randomization unit is each involved psychiatric hospital. Participants in the control group will be assigned to routine WPV management training, participants of the intervention group will undergo the same training while additionally receiving DE training. The DE training will include the following five modules: communication, response, solution, care, and environment (CRSCE). Primary outcomes are objective clinical indicators, which will be extracted from the information systems of the enrolled hospitals. These include the incidence of WPV, injuries caused by WPV, and the use of coercion (physical restraint and seclusion) by nurses. Secondary outcomes, aims at evaluating the effects of DE training on nurses, include the capacity of DE, DE confidence, level of job burnout, and professional quality of life. Data will be collected at baseline (T_0_), at 3 months (T_1_, intervention completed), and at 6 months after intervention (T_2_, follow-up).

**Discussion:**

This study will offer trial-based evidence of the efficacy of a DE training program targeted at WPV among psychiatric nurses. DE training is expected to reduce both the total incidence and negative impacts of WPV, with additional improvements in psychiatric nurses’ coping skills.

**Trial registration:**

Chinese Clinical Trial Registry, ChiCTR1900022211. Prospectively registered on 30 March 2019.

## Background

Workplace violence (WPV) includes any act or threat occurring at a person’s work site involving physical violence, harassment, intimidation, and other threatening or disruptive behaviors [1]. WPV towards healthcare workers has become a warning global issue, with the incidence varying from 8 to 38% [2]. WPV can occur in various manners, ranging from verbal threats to physical assaults. Noticeably, WPV against medical workers is greater in psychiatric wards than in other departments (emergency department, medical and surgical wards, outpatient, and laboratory service) [3]. It has been asserted that, among psychiatric nurses, the incidence of WPV during their career was approximately 100% [4, 5]. Other studies reported that approximately 56.1 to 70% of psychiatric nurses expressed experiences of being physically assaulted by patients at the workplace [6, 7]. In China, WPV-related issues have become increasingly serious, with approximately 82.4 to 94.6% of Chinese psychiatric nurses reporting that they had suffered from at least one type of WPV in the last year, with the incidences of verbal abuse, physical assaults, and sexual harassment being 78.6 to 92.1%, 61.5 to 81.9%, and 18.6 to 42.9%, respectively [8, 9].

The high incidence of WPV in mental health settings has caused a series of negative impacts among nurses, with exposure to WPV usually leading to physical injuries. An investigation by Yang et al., [9] noted that perpetrators, who had physically assaulted psychiatric nurses, had done so by bumping, pushing, gripping, biting, and even punching them. A survey among psychiatric nurses showed that 26% of them were seriously injured due to WPV, sustaining wounds like skin injuries, eye injuries, bone fractures, and permanent disabilities [10]. Moreover, a recent study reported that WPV contributed to increases in sick-leave taking among psychiatric nurses [11]. Besides physical injuries, Needham et al. [12] discovered that WPV also caused certain critical, non-somatic negative effects on psychiatric nurses. Exposure to WPV resulted in bio-physiological (depression, anxiety, and fear), cognitive (thinking of oneself as disrespected, violated, threatened, and robbed of one’s rights), emotional (anger, exhaustion, guilt, and self-blame), and social effects (doubts on job appropriateness and sense of insecurity) among psychiatric nurses, with some participants being diagnosed with post-traumatic stress disorder (PTSD). Approximately 75% of assaulted psychiatric nurses had complained that WPV had caused psychological burden [13]. Studies congruously claimed that WPV was a vital factor leading to anxiety (r = 0.242, *P* < 0.01) and depression (r = 0.115, *P* < 0.01) [13–15]. A recent study verified that WPV was significantly correlated with a higher job burnout level among nurses because the exposure to it led to both depersonalization and emotional exhaustion [9]. Another study showed that, among psychiatric nurses, exposure to WPV increased work-based stress and job burnout, and reduced their professional quality of life as a direct consequence [7].

The high incidence and severe impacts of WPV has subsequently increased public concern around it. Empirical findings summarized WPV as being associated with the characteristics of patients, nurses, institutes, and general society [8, 14, 16–20]. On one hand, patients with mental illnesses, poor treatment adherence, substance abuse, and aggressive behaviors were found to have a higher risk of posing WPV against psychiatric nurses [21]. Furthermore, nurses who had less work experience, less training, lacked de-escalating techniques, engaged in rude behaviors, and were mentally unwell [13, 15], were found to more frequently suffer WPV [19]. Additionally, empirical studies have also found that those wards with low quality environments and poor decorations resulted in patients’ unpleasant experiences and views around being hospitalized, which would be expressed via their WPV [22, 23]. Furthermore, socio-cultural factors set the tone for the overall social atmosphere influencing public attitudes on violence, following which, the acquiescence of violent behaviors from local cultures may have exacerbated WPV incidences against nurses [19].

Having discovered various factors contributing to WPV, strategies reducing its incidence and negative impacts have been developed accordingly. Occupational Safety and Health Administration (OSHA) guideline indicates that WPV prevention program should be based on the simultaneous implementation of organizational measures, administrative measures, and staff training [24]. Interventions targeted at enhancing staffing levels, restructuring the workplace environments, promoting work organization, improving nurse-patient therapeutic relations, and training medical workers have all proven effective in alleviating WPV [19, 20, 25, 26]. Notably, substantial evidence has found that the promotion of improved de-escalation skills among psychiatric nurses is the most widely acknowledged intervention strategy [22, 27–33]. Experts have reached a consensus that de-escalation (DE) technique is the first-line WPV management strategy during early incidence stages [34, 35]. DE refers to a range of skills involving averting conflicts through emotional regulation and self-management techniques [36]. In the psychiatric nursing context, studies have shed light on the contents of DE. It has been proposed that DE should focus on nurse-patient interactions, patient engagements, choosing appropriate intervention times, ensuring mutual safety, confirming patients’ autonomy, limit-setting, and authoritative interventions [37, 38]. Another study by Hallett and Dickens [39], using concept analysis, emphasized that DE was achieved through techniques around self-regulation, communication, assessment, action, and safety maintenance [39]. The application of DE has had positive impacts on improving nurses’ capacities, as well as on nurse-patient relationships, while reducing the use of coercive strategies by nurses (including seclusion, physical restraints, and mechanical restraints). After comparing pre- and post- results of the De-escalating Aggressive Behavior Scale, Nau et al., [40] suggested that the training of DE enhanced student nurses’ performances in dealing with WPV (with scores for untrained = 3.01 vs. trained = 3.61). Another study also found that nurses receiving DE training possessed greater self-perceived confidence than those without, demonstrating that this form of preparation effectively enhanced nurses’ performances by strengthening their confidence levels in dealing with WPV [41]. In addition, Fröhlich et al., [42] highlighted DE training’s role in helping to cultivate a harmonious atmosphere within psychiatric wards by improving patients’ coherence and subjective safety. Most importantly, the application of DE techniques decreases the use of coercive strategies. Empirical studies verified that DE training, targeting psychiatric nurses, reduced the use of physical restraints by approximately 26.4 to 74.0%, and had cut down their likely duration and resultant adverse effects [43]. Current findings have confirmed that DE is a significantly utilized approach in dealing with WPV as well as in reducing the use of coercion, suggesting that DE is an indispensable component of standardized training programs for psychiatric nurses [29, 41, 44, 45]. However, the presented studies all possesses some limitations. First, among most studies, DE training is combined with other components concurrently, such as improved staffing levels, leadership styles, and risk assessments, and, therefore, the actual efficacy of DE itself remains unclear. Second, studies concerning DE provides weak creditability due to their lack of trial-based evidence [46]. Third, the characteristics of the DE training programs used among the current studies varies from one to another because its design needs to be matched to the environmental and socio-cultural factors— hence, the findings of Western studies might not be accurate in China. Last, very few studies simultaneously appraise the effectiveness of DE training via the improvement of nurses’ capacities and objective indicators.

### Objectives

Based on a literature review, and through using the Delphi method, a program has been developed in order to improve nurses’ WPV coping capacities. This program is named after the first letter of each core component, which are Communication, Response, Solution, Care, and Environment (CRSCE), respectively. The aim of this study is to evaluate the effectiveness of a DE training program using the CRSCE core components among Chinese psychiatric nurses.

## Methods

### Trial design

The CRSCE program is a multi-center, single blinded, cluster randomized controlled trial with a 6-month follow-up period. All stages of this trial are in accordance with the CONSORT guidelines.

### Settings and participants

This trial will be conducted among 6 major public psychiatric hospitals in Guangdong, China. The involved psychiatric hospitals are Guangzhou Mental Health Center (GZ), Shenzhen Mental Health Center (SZ), the Third Hospital of Foshan City (FS), the Second Hospital of Huizhou (HZ), Shantou Mental Health Center (ST), and the Third Hospital of Meizhou (MZ). The number of wards (secured and non-secured) and nurses of the involved hospitals are shown in Table 1*.* This study has gained ethical approval from the IRB of GZ. Executives from the involved institutes will be informed and asked for their permission to conduct the study, with the help of the nurses. Informed consent will be obtained from all participants before they complete the surveys.

**Table 1 Tab1:** Numbers of wards and nurses of recruited hospitals (secured and non-secured)

Hospital	Non-secured ward			Secured ward		
	Number of wards	Number of beds	Number of nurses	Number of wards	Number of beds	Number of nurses
GZ	3	120	65	14	865	322
SZ	1	45	18	10	623	297
FS	1	106	29	8	816	243
HZ	1	44	20	7	906	291
ST	3	60	46	8	620	231
MZ	1	60	20	7	700	220

### Inclusion criteria

Aged from 18 to 60 years.

Registered nurses engaging in mental healthcare.

Are employed as full-time nurses.

### Exclusion criteria

Student nurses and nursing interns.

Personnel taking refresher trainings at engaged wards.

### Interventions

Participants in the control group will receive routine WPV management training, participants of the intervention group will undergo the same training while additionally receiving CRSCE-based training. CRSCE is a 5-module training program, composing 104 learning hours, which will be completed in 3 months. The modules, objectives, and learning hours of routine WPV management training and the CRSCE program are presented in Table 2.

**Table 2 Tab2:** Modules, objectives, and learning hours of routine WPV management training and CRSCE

Module		Content	Objects	Hours		Routine WPV management training	CRSCE training
				Lecture	Practice		
Routine WPV management training		Basic Communication Skills of Nursing	To understand the concept of communication skills and its attributes To understand different types of communication skills To learn how to interact with patients in practice	4	–	**✓**	**✓**
		Communication Skills in Mental Health Care	To identify the attribute of communication skills in mental health care To distinguish the difference of communication skills between mental health and general nursing To learn how to interact with psychiatric patients	4	4	**✓**	**✓**
		Risk Assessment of Violence	To understand the types of WPV To learn how to use different assessment tools To discuss advantage and disadvantage of assessment tools	4	–	**✓**	**✓**
		The Ethic and Law in Metal Health Care	To discuss the ethical issues in mental health care To discuss how nurses to balance the ethical issues and law in mental health care	4	–	**✓**	**✓**
		De-escalation	To know the concept of De-escalation To identify the attributes of De-escalation To discuss the key components contribute to successful de-escalation	4	–	**✓**	**✓**
		Practical WPV coping skills	To learn the breakaway techniques, holding methods To learn the control and restraint methods	4	8	**✓**	**✓**
CRSCE training	Communication	How to Build the Therapeutic Nurse-Patient Relationship	To identify the factors that influence therapeutic relationship To identify the key components of building the therapeutic relationship with patients To learn how to build therapeutic nurse-patient relationship using communication skills	4	4	**NA**	**✓**
		The Communication Skills with Aggressive Patients	To learn the communication skills with aggressive patients	4	4	**NA**	**✓**
	Response	The Early Stage Signal of WPV	To identify the early stage signal of WPV To discuss and learn what a nurse should do when he/she has identified a patient is in WPV early stage	4	4	**NA**	**✓**
		What Is Your FIRST Reaction When WPV Happens?	To recall nurses’ memories of facing violence To share nurses’ experience of coping with violence To refresh and discuss the appropriate method to manage WPV	4	–	**NA**	**✓**
		When WPV Happens, What Should We Do?	To learn how to response WPV To discuss the alternatives of WPV	4	2	**NA**	**✓**
		What Is the Influence of WPV on You?	To discuss and share the influence of WPV on individual	4	–	**NA**	**✓**
	Solution-Focused Technique	Cognitive Positive Psychology	To learn the concept of cognitive positive psychology and how to use it in clinical work	4	4	**NA**	**✓**
		The Concept and Principle of Solution-Focused Technique in Nursing	To learn the concept and principle of solution-focused technique	4	–	**NA**	**✓**
		The Five Stages of Psychological Intervention of Solution-Focused Technique and Its Application	To identify the five stages of psychological intervention of solution-focused technique To learn using the five stages of psychological intervention in practice	4	2	**NA**	**✓**
	Care	The History and Development of Humane Care Service	To understand the history and development of humane care service To identify the key elements of humane care service	4	–	**NA**	**✓**
		The Relationship Between Humane Care Service and WPV	To discuss the relationship between humane care service and WPV To learn proving humane care to aggressive patients	4	4	**NA**	**✓**
		The Humane Care Service in Mental Health Care	To identify the humane care service in mental health care To discuss what nurses can do to provide the humane care service to psychiatric patients	4	4	**NA**	**✓**
	Environment	The Innovation of Environment in Mental Health Care	To understand the concept of environment in mental health care To understand the change process and development of environment in mental health care	8	4	**NA**	**✓**
		Evidence Base Practice: The Relationship Between Ward Environment and WPV	To discuss how environment affects the WPV To find out the environmental hazards of WPV through literature review To implement achievable improvement of ward environment	8	8	**NA**	**✓**
**✓**: Included modules **NA**: Not Available				Total Learning Hours		**36 h**	**140 h**

### Outcomes

Primary outcomes are objective clinical indicators of the included wards, which will be extracted from the hospital information systems and their annual reports. The objective indicators include the frequency of WPV, injuries caused by WPV, and the use of coercion (physical restraint and seclusion). The objective indicators will be calculated as follows:
monthly WPV frequency = monthly numbers of WPV event / total monthly patient days × 1000 ‰;monthly frequency of injuries caused by WPV = monthly numbers of injuries caused by WPV / total monthly patient days × 1000 ‰ and;monthly frequency of physical restraint (or seclusion) = monthly numbers of patient days of physical restraint (or seclusion) / total monthly patient days × 1000 ‰.

Secondary outcomes are collected in order to evaluate the impacts on the nurses. The De-escalating Aggressive Behavior Scale (DABS), Confidence in Coping with Patient Aggression Instrument (CCPAI), Maslach Burnout Inventory-General Survey (MBI-GS), and Professional Quality of Life Scale (Pro QOL), will all be used to evaluate the capacity of DE, confidence of DE, level of job burnout, and professional quality of life, respectively. The above survey instruments will be used after obtaining licenses. The flow chart of this study is presented in Fig. 1.

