### Sample size

Sample size estimation is based on monthly frequency of WPV. Using the study by I. et al., (2004), we set a significant change of 12.1% (decreased from 17.8% by 5.70%), alpha error of 0.05, beta error of 0.20, the estimated number (N _simple_) of monthly records is 29 per group for simple randomized control trial [47]. The intra-class correlation coefficients (ICC), explains the inflation factor of cluster randomized controlled design trial, is set as 0.05 in proposed study [48]. Based on the numbers of wards of MZ and HZ (*n* = 8), the minimum number of 6-month follow-up record (m) is 48. The sampling size of cluster randomized controlled trial (N _cluster_) is calculated as: N _cluster_ = [1 + (m^− 1^) * ICC] * N _simple_ ≈ 98. The minimum number of recruited hospitals of each group (N) is calculated as: N = N _cluster_/ m ≈ 2.04 < 3, suggesting at least 3 hospitals per group.

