### Statistical methods

Statistical analysis will be performed using SPSS version 22.0 software (SPSS Inc., Chicago, IL, USA). Descriptive statistics will be reported as frequencies and percentages, if applicable. The Shapiro-Wilk test will be used in order to examine the distributions of the continuous outcomes. Quantitative variables will be presented using means and standard deviations or as the median and interquartile range. A Student’s t-test, Mann-Whitney U test, Chi-square test, or Fisher’s exact test will be adopted to compare the groups according to their normality distributions. Additionally, a repeated ANOVA will be used to explore the effectiveness of the CRSCE training program and further regression analysis will be performed, if appropriate. The statistical significance will be set at *P* < 0.05, two tailed, with a 95% confidence interval (*CI*).

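### Three or four unranked primary indicators share one unadjusted 0.05 threshold, with no rule on whether one or all must succeed, while the trial is sized on WPV frequency alone

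*Protocol article*

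**What the plan says.** - **Outcomes.** The primary outcomes are ward-level indicators taken from hospital records: "The objective indicators include the frequency of WPV, injuries caused by WPV, and the use of coercion (physical restraint and seclusion"). There are three formulas, each a monthly rate per 1000 patient-days. Restraint and seclusion share the third: "monthly frequency of physical restraint (or seclusion) = monthly numbers of patient days of physical restraint (or seclusion"). No indicator is placed above the others.
- **Sample size.** "Sample size estimation is based on monthly frequency of WPV", with "alpha error of 0.05, beta error of 0.20". No allowance is made for the other primary indicators.
- **Statistical methods.** "The statistical significance will be set at" P < 0.05, two tailed. This is one general threshold. No hierarchy, division of alpha, or any-or-all rule accompanies it.
- **Discussion.** The hypothesis is that WPV, injuries and coercion will all fall. What to conclude if only some of them fall is not addressed.

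**The concern.** The aim is a verdict on whether the CRSCE programme is effective. With several co-equal primary indicators and one threshold, that verdict depends on a rule the article does not give. If one significant indicator is enough, the overall false-positive rate exceeds the 5% on which the trial was sized. If all must be significant, the error rate is controlled, but the sample size, worked out for WPV frequency alone, says nothing about the power to achieve that.

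A mixed result is a realistic prospect. The article's own limitations concede that training may raise awareness of WPV and so change how it is reported. Recorded WPV could then rise while restraint falls. As written, the plan allows that to be read as success or as failure once the data are known.

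**Working it through.** **The plan's own figure.** The article states no familywise error rate, so there is none to reproduce. Its sample size for the single outcome, WPV frequency, starts from 29 monthly records per group, ICC 0.05 and m = 48:

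- Design effect: 1 + (48 − 1) × 0.05 = 3.35.
- N cluster: 3.35 × 29 = 97.15, rounded up to 98.
- Hospitals per group: 98 / 48 = 2.04, so 3.

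This step reproduces. The starting value of 29 cannot be derived from the article because no SD is given. That is a separate matter, and the error rates below do not depend on it.

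**Inputs.** Number of primary indicators k = 3 (coercion as one) or k = 4 (restraint and seclusion separate), from Outcomes. Two-sided alpha 0.05 per test, so 0.025 in the favourable direction, from Statistical methods. Each test is assumed to hold its nominal level.

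**Case A: any one significant indicator suffices.**

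Under independence:

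- Either direction: 1 − 0.95^3 = 14.3%; 1 − 0.95^4 = 18.5%.
- Favourable direction only: 1 − 0.975^3 = 7.3%; 1 − 0.975^4 = 9.6%.

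Upper bound under any dependence:

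- Either direction: 3 × 0.05 = 15%; 4 × 0.05 = 20%.
- Favourable direction only: 3 × 0.025 = 7.5%; 4 × 0.025 = 10%.

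With a common positive correlation between the test statistics (simulation of equicorrelated normal statistics, 1,000,000 draws; the correlations are assumed, as the article gives none):

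| Correlation | k = 3, either | k = 3, favourable | k = 4, either | k = 4, favourable |
|---|---|---|---|---|
| 0.3 | 13.6% | 6.8% | 17.5% | 8.8% |
| 0.5 | 12.5% | 6.3% | 15.6% | 7.8% |
| 0.7 | 10.9% | 5.5% | 13.0% | 6.5% |
| 0.9 | 8.3% | 4.2% | 9.4% | 4.7% |

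The comparators for one two-sided test are 5% in either direction and 2.5% in the favourable direction.

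**Case B: all indicators must be significant.** The probability that all are falsely significant cannot exceed that of any one of them, so it is at most 5% (2.5% favourable). There is no inflation.

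**What splitting alpha would cost.** With k = 4, Bonferroni gives 0.05 / 4 = 0.0125 per test.

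- *By the article's sizing method.* With the SD implied by 29 per group at 80% power, power at 29 per group falls from 80% to about 62%. Restoring 80% needs 42 per group; 42 × 3.35 = 140.7, so 141; 141 / 48 = 2.94, still 3 hospitals per group.
- *If the analysis were a t-test on six hospital means (4 df).* This is an assumption, since Statistical methods does not specify it. The standardised effect implied by 29 per group is (1.960 + 0.842) × √(2/29) = 0.736. Effective records per arm are 3 × 48 / 3.35 = 43.0. The noncentrality is 0.736 × √(43.0/2) = 3.41. Power is about 72% at 0.05 and about 37% at 0.0125.

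**The case against.** **Scope.** This is a condensed article, and multiplicity rules are commonly left to the analysis plan, which is not shown. That is fair as far as the silence goes, and sizing on one of several primary outcomes is common and not in itself an error. But the article itself fixes the unranked primary set, the single sizing outcome and the general 0.05 threshold. A rule held elsewhere could settle the ambiguity; the choice of primary outcome still belongs in the protocol.

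**The success rule.** A reader might infer that one positive indicator would be taken as proof of effectiveness. The article does not say so. The Discussion states the hypothesis jointly, which fits an all-must-succeed rule at least as well. This objection stands: the inflation is conditional on the any-one reading, which the plan neither states nor excludes.

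**The size.** A reader might take 18.5% as the chance of wrongly declaring the programme effective. It is not. It counts significant differences in either direction, including apparent harm, and it is the value under independence, not a ceiling. A false favourable result has probability 9.6% for four independent indicators.

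**The count.** The prose lists three indicators and there are three formulas. Four is a fair reading of the restraint-or-seclusion wording, but it remains a reading.

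**Splitting alpha instead.** By the article's own arithmetic, Bonferroni would still need only three hospitals per group, so it cannot be dismissed on the plan's own inputs. The much larger loss of power appears only under the hospital-level assumption.

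**Conclusion.** The point holds in a conditional form. The protocol leaves three or four primary indicators unranked, sizes the trial on one, and applies one unadjusted threshold without saying what combination of results means success.

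If any one suffices, the familywise error under independence is about 14% to 19% in either direction. For a false favourable result it is about 7% to 10%, roughly three to four times the 2.5% of a single test (7.3 / 2.5 = 2.9; 9.6 / 2.5 = 3.9). Positive correlation, which is plausible for these outcomes, lowers these figures. If all must be significant, there is no inflation.

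The figures also assume that each test holds its nominal 5%, which ordinary t-tests or ANOVA on clustered records from six hospitals may not. The matter should be settled before outcome data are seen. It does not by itself invalidate the design.

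**What to change.** Name monthly WPV frequency per 1000 patient-days, the outcome already used for sizing, as the single primary outcome. Then choose one of two options for the rest:

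- test injuries, restraint and seclusion after it in a pre-specified fixed order, each at two-sided 0.05 and only if the preceding test succeeded; or
- report them as secondary outcomes with estimates and confidence intervals.

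State in the same place whether restraint and seclusion are one indicator or two. Either option holds the familywise error of the confirmatory tests at 5%, provided that each test is itself valid.

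The cost is one sentence in the protocol and a registry update, with no extra hospitals or data. The price is that injuries, restraint and seclusion lose stand-alone primary status.
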